# Short-stretch inelastic compression bandage in knee swelling following total knee arthroplasty study (STICKS): study protocol for a randomised controlled feasibility study

**DOI:** 10.1186/s13063-015-0618-0

**Published:** 2015-03-11

**Keywords:** Knee replacement, Arthroplasty, Compression bandage, Enhanced recovery, Fast track

## Abstract

**Background:**

Enhanced recovery programmes in total knee arthroplasty are well established. Post-operative knee swelling is common and impairs early post-operative function. The use of a short-stretch, inelastic compression bandage is hypothesised to reduce knee swelling and improve pain and early function. A study was designed to test feasibility with a view to informing a larger, future trial and to provide preliminary data.

**Discussion:**

Enhanced recovery programmes have revolutionized the management of total knee arthroplasty. There is a paucity of clinical data regarding the efficacy of compression bandages. Large, randomised controlled trials are uncommon in orthopaedic surgery. The results of this study will provide feasibility and preliminary data prior to the construction of a larger, multicentre study.

**Trial registration:**

The study was registered with Current Controlled Trials (ISRCTN86903140) on 30 May 2013.

## Background

Total knee replacement is a common and highly successful operation in the management of osteoarthritis. The evolution of enhanced recovery programmes over the last 15 years has reduced hospital stay and morbidity, without increasing readmission rates [1,2].

Post-operative knee swelling is a common problem following total knee replacement. This is largely due to intra-articular bleeding and inflammation of periarticular tissues [3]. Knee swelling results in decreased functional performance as a result of quadriceps weakness [4] and as a result of arthrogenic reflex inhibition due to pain [5]. The resulting decrease in functional performance can delay rehabilitation and affect length of stay and patient-reported outcomes [6,7]. Excessive knee swelling is also associated with increased rates of dehiscence and infection in surgical wounds [8].

Various techniques have been utilised to reduce intra-articular bleeding, including modification of surgical technique [9], tourniquets [10], medication [11] and rehabilitation protocols [12]. Post-operative methods include the use of a cold compress [13], cryotherapy [14], elastic bandaging [15] and compression bandages [16,17].

However, there is a paucity of clinical data regarding the use of compression bandages with heterogeneous methodology. Andersen *et al*. utilised a compression bandage consisting of a double layer of soft padding and an outer elastic adhesive dressing compared with standard bandage in a randomised controlled trial of 48 patients [16]. The bandage was combined with local anaesthetic infiltration. The intervention group had significantly reduced pain at 8 hours compared to a control group. There was no difference in length of stay. As this was an acute pain study, range of motion, swelling and quality of life were not assessed.

A randomised controlled trial of 60 patients undergoing unicondylar knee arthroplasty found no difference in swelling and post-operative pain in patients who received a modified Robert-Jones type bandage compared to a standard wool and crepe bandage when assessed at 24 h and 48 h post-operatively [18]. Conversely, a non-randomised study of 150 patients undergoing total knee arthroplasty found a compression bandage to be advantageous, with improvements in total range of motion and length of stay when compared to wool and crepe bandages [12].

Munk *et al*. randomised 88 patients to receive either an elastic medical compression stocking or no stocking for 4 weeks after total knee arthroplasty [19]. The main outcome measures were knee swelling, knee flexion and pain scores. The study did not find any clinical effect between the two groups. However, the stocking was applied the day after surgery when it was documented that 70% of the swelling had already occurred.

Therefore, the efficacy of compression bandage therapy after total knee arthroplasty remains unclear due to varying methodology and small sample sizes. The efficacy of compression bandaging in the treatment of venous ulcers and lymphoedema is encouraging [20,21]. With regard to total knee arthroplasty, there are two main mechanisms that cause post-operative swelling. The first is an increase in vascular permeability as a result of the release of histamine and histamine-like substances causing the capillary network to allow more electrolytes and plasma proteins into the tissues as a direct response to trauma [8]. This causes an imbalance in homeostasis and a net movement of fluid into the interstitial space from the vascular space. This response is short lived but deleterious. Secondly, vascular injury from the surgery causes bleeding, which leaks into the tissues until plugged by thrombus [8]. Whilst the mechanisms of compression therapy are poorly understood, it is believed that the application of external compression causes a decrease in hydrostatic pressure by aiding venous return as a result of moving blood from the superficial to deep venous system and by improving the efficacy of the calf muscle pump. This allows movement of fluid from the interstitial space. It also aids lymphatic drainage, and a resultant hyperaemic response improves arterial blood flow [22]. With regard to the type of bandage, inelastic compression bandages have been found to have a low, tolerable resting pressure but a more effective activation of the deep venous system and calf muscle pump with ambulation compared to the elastic counterparts [23].

It is hypothesised that the use of a compression bandage in total knee arthroplasty will therefore reduce lower leg swelling by improving venous return post-operatively. This improvement will improve knee extension strength and reduce pain inhibition, allowing earlier, effective rehabilitation and an improvement in length of stay and patient reported outcome measures.

To test this hypothesis, a large, randomised controlled trial is required. The aim of this current study is to test the feasibility of the methodology and gather data to inform a larger future trial. The secondary objective is to perform a small-scale trial to provide preliminary data.

## Methods/design

The study is a prospectively enrolled, randomised controlled feasibility study conducted at two hospital sites within the Northumbria Healthcare NHS Foundation Trust. The study has been approved by the Newcastle and North Tyneside Research Ethics Committee (13/NE/0137), and all patients will provide written, informed consent. The study has been registered with Current Controlled Trials (ISRCTN86903140) and is sponsored by Northumbria Healthcare NHS Foundation Trust.

### Participant recruitment

A total of fifty consecutive patients selected for total knee arthroplasty will be enrolled in the study. Due to insufficient data in the literature to determine a clinically relevant change in outcome measures, the sample size is based on the ability to calculate a mean and standard deviation in these measures to allow an accurate power calculation for the future trial. The sample size conforms to guidelines on feasibility studies in the literature and is large enough to additionally provide preliminary data [24].

### Study duration

The study started recruiting in November 2013, and data collection is expected to finish in December 2014. This timeframe is based on 2 months initial set-up, 6 months recruitment and 6 months follow-up. Six months recruitment assumes approximately two patients per week or one patient per operating surgeon. Based on joint registry data, this assumes an approximate inclusion rate of 66% based on the two operating surgeons’ caseloads.

### Inclusion /exclusion criteria

The inclusion criteria for the study include (i) primary total knee arthroplasty for osteoarthritis, (ii) age over 18, and (iii) able to provide written, informed consent.

Exclusion criteria include (i) peripheral vascular disease characterised by an ABPI <0.8, (ii) peripheral neuropathy, (iii) BMI >35, (iv) revision knee arthroplasty, (v) unicondylar or patellofemoral joint knee arthroplasty or (vi) high dose anticoagulation. The majority of criteria have been established to reduce confounding variables associated with post-operative swelling in knee arthroplasty or due to contraindications with the compression bandage.

### Consent

The patient is given an information sheet regarding the trial after being listed for knee joint arthroplasty. Any questions are answered by a good clinical practice (GCP)-trained research nurse before the patient is consented into the trial. The patient is given at least 24 hours to make this decision following initial supply of information.

### Patient allocation

The patient is randomised to the intervention on the day of surgery by electronic distance randomisation using the website www.sealedenvelope.com. The randomisation process is done in permuted blocks to allow even balancing of the groups. Patients will be allocated to the standard care group or the compression bandage group as outlined below.

**Figure 1 Fig1:**
[figure not shown]
**Standard wool and crepe bandage.**

The bandage and wound catheter are removed at 24 hour leaving the hydrocolloid wound dressing *in-situ*. This dressing stays on until the clips are removed at 10 to 14 days and prevents any contamination of the wound, for example, during the knee swelling measurements. A cryocuff is used after 24 hours.

Physiotherapy starts on the day of surgery. Focus initially is on first time mobilisation, quadriceps strengthening exercises and passive full extension. Following this, patients are seen at least twice daily by the physiotherapist, and range of motion, gait re-education and lower limb strengthening techniques are employed every day until discharge from hospital. Patients are seen weekly in an outpatient physiotherapy class if required until they are independently walking, have full passive extension and a range of motion in the knee from 0 to 90 degrees.

### Intervention group

The compression bandage is applied over the hydrocolloid surgical wound dressing. A soft inner layer (Soffban, BSN Medical Ltd, Brierfield, UK) is applied from the toes to the groin on the affected leg with a 50% overlap of bandage. Following this the outer compressive layer bandage (Actico bandage, Activa Healthcare Ltd, UK) is applied firmly over the top, again with a 50% overlap of bandage. The bandage is pulled to full stretch before it is wrapped around the leg to ensure adequate compression in the application (Figure 2). A short-stretch, inelastic compressive bandage has been chosen because it is tolerable overnight due to its low resting pressure, yet produces high pressure with movement to greatly improve the efficacy of the calf muscle pump. The bandage is applied from the toes upwards. The application of bandage from thigh to groin requires removal of the tourniquet first and so the leg is kept elevated until the bandaging is complete. To ensure homogeneity in bandage application, the operating surgeons were shown a training video on correct application of the bandage and were given a tutorial on bandage application with real life bandage application and feedback. Correct bandage application was checked throughout the trial by the lead author and research nurse. The bandage is removed at 24 hours post-surgery leaving the hydrocolloid wound dressing *in-situ*. Otherwise the protocol follows that of the standard care group.

**Figure 2 Fig2:**
[figure not shown]
**Short-stretch, inelastic compression bandage.**

### Outcome measures

#### Study feasibility

Processes key to the future study will be analysed. Recruitment, retention and refusal rates will be calculated. The proportion of patients undergoing primary total knee arthroplasty who did not meet the eligibility criteria will also be calculated to ensure this is not too restrictive.

Resource allocation will be determined by calculating the time required for the recruitment and follow-up process. This will allow accurate resource allocation with regard to clinical research nurse and physiotherapy input.

Bandaging skill acquisition training video, ease of application and tolerance of the compression bandage will be determined from the operating surgeons and patients. Potential adverse risks associated with the use of the compression bandage such as pain, wound dehiscence and blistering will be recorded and rates calculated.

Qualitative feedback will be provided by the research team and clinical staff to determine any potential problems associated with the methodology with particular reference to the ease in obtaining the secondary outcome measures. The data will be analysed to calculate the completion rate of each outcome measure. A trial steering committee will meet before, half way through, and after the trial to discuss this feedback. The trial management group will complete day to day monitoring of the trial, consisting of the chief and principle investigator, the clinical research nurse and the research physiotherapists.

#### Feasibility of outcome measures

##### Swelling

Circumference or girth of the knee has been shown to have acceptable reliability for determination of gross changes in knee swelling in patients post-surgery [25]. Knee swelling is measured using the circumference of the knee at the mid-portion of the patella with the knee in full extension. Measurements are then taken 10 cm proximal to the superior pole of the patella (thigh) and 10 cm distal to the inferior pole of the patella (calf). The skin is marked at these points and the tape measure placed circumferentially around the limb, at and distal to the level of the mark). Measurements are in centimetres to one decimal place. Pre-operative values are taken on the day of surgery, every post-operative day after bandage removal until discharge and at 6-week follow-up.

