##### Range of motion

Active range of motion at the knee is measured using a goniometer. The inter-tester reliability and validity of this method previously have been shown to be high [26]. The patient is positioned supine, with the hip and knee in the neutral position. The femur is stabilised to prevent rotation with a hand. The goniometer is placed on the lateral epicondyle of the femur, with the proximal arm on the lateral midline of the femur in line with the greater trochanter, and the distal arm on the lateral midline of the fibula in line with the lateral malleolus. Active flexion and extension values are recorded. Pre-operative values are taken on the day of surgery, every post-operative day after bandage removal until discharge and at 6-week follow-up.

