##### Rest pain

At-rest pain scores from 0 to 10 using a visual analogue scale are assessed every day, prior to and after physiotherapy in hospital. The visual analogue scale is a simple and reliable method of recording pain and has been validated in lower limb arthroplasty [27]. Pre-operative values are taken on the day of surgery, and further values assessed on every post-operative day until discharge and at 6-week follow-up.

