##### Length of stay

This is calculated from the patient’s admission and discharge dates and reflects midnights in hospital.

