### Statistical analysis

A secure Excel database will be used to record data (Microsoft Inc, Albuquerque, NM, USA). Statistical analysis will be performed using SPSS version 23.0 (SPSS Inc, Chicago, IL, USA).

A power calculation will be performed based on the mean and standard deviations of knee swelling values collected from this preliminary data to inform a larger, future trial. A treatment effect of a 3-cm reduction in swelling based on previous literature will be used, utilising a 1-cm error of measurement and a 2-cm clinical minimal relevance [19]. The risk of a type 1 error will be set at 0.05 and a type II error at 0.20. The retention rate from feasibility data will be incorporated into the final sample size number to allow for possible patient drop-out. The recruitment rate and resource allocation hours can then also be applied to the final sample size required to plan the future trial requirements.

For each outcome measure (knee swelling, range of motion, visual analogue score, EQ-5D score, Oxford knee score) the two groups will be compared at each applicable set time point (pre-operative, day 1, day 2, 6 weeks, and 6 months). The difference from pre-operative measurement will also be used to reduce the impact of confounding factors between groups. A 95% confidence interval of the group differences will be calculated for each variable. A Kolmogorov-Smirnov goodness of fit will be used to determine the distribution. If the distributions are equal, Student’s *t*-test for independent samples will be used. The Welch correction will be used if variances are unequal. If the distributions are unequal, the Mann-Whitney *U* test will be used. Significance will be denoted at *P* <0.05.

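### In-hospital measurement ends at discharge but the arms are compared at day 2, so that comparison is open to selection bias if patients go home before it

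*Protocol article*

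**What the plan says.** Measurement. Under Swelling, values are taken pre-operatively, then "every post-operative day after bandage removal until discharge and at 6-week follow-up". Range of motion follows the same schedule: "Pre-operative values are taken on the day of surgery, every post-operative day after bandage removal until discharge and at 6-week follow-up". Under Rest pain, "further values assessed on every post-operative day until discharge and at 6-week follow-up". All three therefore have an in-hospital series that ends when the patient goes home, followed by a 6-week value that does not depend on discharge. The article describes no day-2 measurement for a patient who has already left.

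Analysis. For each outcome "the two groups will be compared at each applicable set time point (pre-operative, day 1, day 2, 6 weeks, and 6 months"), using a t-test, its Welch version or a Mann-Whitney test. The Abstract also names day 2 for swelling, motion and pain. The difference from the pre-operative value is used as well.

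Discharge. Length of stay is itself an outcome ("This is calculated from the patient’s admission and discharge dates and reflects midnights in hospital"). The Background expects the bandage to reduce swelling and pain, "allowing earlier, effective rehabilitation and an improvement in length of stay and patient reported outcome measures". No expected mean or distribution of stay is given.

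Missing values. Under Study feasibility, a completion rate will be calculated for each outcome measure.

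**The concern.** Whether a patient has a day-2 value depends on whether that patient is still in hospital, which is decided after randomisation. On the trial's own account, swelling and pain influence the length of stay and the bandage is meant to shorten it. The setting is an enhanced-recovery pathway, and the Background says such programmes have reduced hospital stay, so discharge before the day-2 measurement is plausible.

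If early leavers are the less swollen patients and there are more of them in the bandage arm, the patients remaining at day 2 are more swollen than their randomised arm as a whole, and more so with the bandage. A comparison of observed values then understates a benefit. Using the difference from the pre-operative value does not cure this, because the selection acts on post-operative recovery. The matter is relevant to a feasibility study because testing the methodology for the larger trial is its main aim, and a measurement window that discharge can cut short would carry over.

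**Working it through.** The plan gives no figure to reproduce here: no length of stay, no share leaving before day 2 and no SD. The check therefore has two parts.

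**1. The schedule set against the analysis**

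| Time | Measured | Depends on discharge? |
|---|---|---|
| Pre-operative | Day of surgery | No |
| Day 1 | Swelling and motion after bandage removal ("The bandage is removed at 24 hours post-surgery leaving the hydrocolloid wound dressing"); pain daily | Only if a patient left before that measurement |
| Day 2 | Only if still in hospital | Yes |
| 6 weeks | Follow-up | No |

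The Oxford knee score and EQ-5D, taken pre-operatively and at 6 months, are outside the problem.

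**2. Possible size**

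Inputs from the article: 50 patients, about 25 per arm (equal allocation is inferred from the aim of evenly balanced groups).

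Inputs assumed:
- SD of swelling 2 cm and true day-2 effect 1 cm in favour of the bandage;
- correlation of day-1 with day-2 swelling 0.8;
- correlation of early discharge with low day-1 swelling ρ = 0.3 or 0.5, so the correlation with day-2 swelling is r = 0.8ρ = 0.24 or 0.40;
- a share p of each arm, those furthest along in recovery, leaves before the day-2 measurement.

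For normal variables, the mean of those still measured exceeds the mean of the full arm by SD × r × λ(p), where λ(p) = φ(q)/(1 − p) and q is the normal quantile of p. The bias in the group difference is

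SD × r × [λ(p bandage) − λ(p control)].

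Values of λ: 5%, 0.109; 10%, 0.195; 15%, 0.274; 20%, 0.350; 30%, 0.497; 40%, 0.644.

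| Early discharge, control v bandage | Difference in λ | Observed effect, ρ = 0.3 | Observed effect, ρ = 0.5 |
|---|---|---|---|
| 5 v 15% | 0.166 | 1 − 0.48 × 0.166 = 0.92 cm | 1 − 0.80 × 0.166 = 0.87 cm |
| 10 v 30% | 0.302 | 1 − 0.48 × 0.302 = 0.86 cm | 1 − 0.80 × 0.302 = 0.76 cm |
| 20 v 40% | 0.294 | 1 − 0.48 × 0.294 = 0.86 cm | 1 − 0.80 × 0.294 = 0.76 cm |
| Equal rates | 0 | 1.00 cm | 1.00 cm |

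The multipliers are 2 × 0.24 = 0.48 and 2 × 0.40 = 0.80. The understatement runs from about 8% to 24%. It is zero if ρ = 0, if nobody leaves before day 2, or if equal shares leave.

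Against sampling error: at 20 v 40%, 25 × 0.8 = 20 and 25 × 0.6 = 15 patients remain. The standard error is 2 × √(1/20 + 1/15) = 0.68 cm. The bias of 0.14 to 0.24 cm is 0.21 to 0.34 of that.

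Effect on the SD: among those still measured, the SD is multiplied by √(1 − r²λ(λ − q)). At 40% and r = 0.40, with q = −0.253, this is √(1 − 0.16 × 0.644 × 0.897) = 0.953, a shrinkage of 4.7%. At 5% and r = 0.24, with q = −1.645, it is √(1 − 0.0576 × 0.109 × 1.754) = 0.994, about 0.6%. The range is roughly 1 to 5%.

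In this set-up early discharge is linked to day-2 swelling only through day-1 swelling. A model that conditions on the day-1 value therefore recovers the 1-cm effect; comparing observed day-2 values does not.

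**The case against.** The strongest reply is that no bias has been shown. It needs patients to leave before the day-2 measurement, more of them in one arm, and discharge related to swelling. The article gives no length of stay. Bandage and wound catheter come off at 24 hours and physiotherapy is at least twice daily until discharge, so missing day 2 means leaving after about one night, and nothing in the text supports 20% or 40% doing so. This stands. A reader might infer that the day-2 comparison is biased; the documents support only that it is open to bias under stated conditions.

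A reader might also infer that nothing is measured after discharge. That is wrong, since the 6-week value is in the same sentence. Nor do the documents show that the future power calculation is distorted: the Statistical analysis section does not say which time point supplies the SD, and the SD effect is small in any case.

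It is also fair that the assumed bias is a fraction of one standard error and below the 1-cm measurement error the plan uses, that efficacy is a secondary, preliminary objective, and that completion rates will be calculated. These points lower the weight of the concern without removing it. Completion rates count missing values but do not correct the comparison, and are not said to be split by arm or reason.

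Finally, missing-data handling may sit in an analysis plan that is not shown. But the measurement rule and the day-2 comparison are both fixed in the article, and no later plan can supply a value that was never taken.

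**Conclusion.** The concern holds in a conditional form. The article fixes a day-2 comparison of observed values while ending in-hospital measurement at discharge, an event the bandage is hypothesised to bring forward. If patients leave before the day-2 measurement, more often in the bandage arm, and leaving goes with lower swelling, a benefit would be understated. The 8 to 24% range for a 1-cm swelling effect belongs to the assumed inputs, not to anything in the article. The same reasoning applies to motion and pain, but their size was not calculated. This is worth correcting because the remedy is cheap and the study exists to test methodology. It does not threaten the feasibility objectives.

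**What to change.** Replace the separate day-1, day-2 and 6-week tests for swelling, range of motion and rest pain with one likelihood-based repeated-measures model for each outcome: arm by time, with the pre-operative value as covariate. Include every randomised patient with any follow-up, so that day-1 and 6-week values inform missing day-2 values. Report, by arm, the number measured and the number already discharged at day 2.

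Taking the day's measurement before anyone leaves on day 2 is arguably already required by the daily schedule and needs at most a clarifying line. Naming day 1 as the source of the SD for the power calculation is optional.

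The cost is a change of analysis wording and one extra line of reporting, with no additional data. The downside is a slightly more complex model that relies on missing at random: discharge may depend on recorded values, but not otherwise on the unseen day-2 value.
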